## Abstract

**Background:**

Moisturisers prevent and treat dry skin. They can also protect sensitive skin, improve skin tone and texture, and mask imperfections. Herbal medicines or their extracts have been available as topical formulations and cosmetics. *Arctium lappa L. (Asteraceae)* has been used to treat inflammatory disorders and various skin problems. It could be a candidate herbal medicine for treating dry skin condition.

This study aims to establish the efficacy and safety of a proposed herbal moisturising cream containing *Arctium lappa L.* seed extract, which has been approved by the Korean Ministry of Food and Drug Safety for use in cosmetics.

**Methods/Designs:**

This study is a randomised, double-blind, placebo-controlled study with two parallel groups (proposed herbal moisturising cream vs. placebo cream). We will recruit 66 healthy male and female participants, aged 20 to 65 years, who have been diagnosed with dry skin conditions. Participants will be randomly allocated to receive either the proposed herbal moisturising cream or a placebo cream for four weeks. Each participant will be examined for signs and symptoms before and after using the cream. Skin hydration, sebum (oily secretion) levels and transepidermal water loss (TEWL; constitutive loss of water from the skin surface) will be assessed. Participants will also be asked to fill out a health-related quality of life questionnaire. Safety will be assessed using blood tests, urine analysis, a pregnancy test, and the assessment of vital signs.

**Discussion:**

This trial will utilise high-quality methodologies in accordance with both consolidated standards for reporting trials guidelines and the guidelines for clinical trials of cosmetics products that are aimed at expressions and advertisement approval in Korea. It will evaluate the clinical efficacy and safety of a proposed herbal moisturising cream containing *Arctium lappa L.* seed extract to treat dry skin conditions and provide itch relief. Moreover, we will also employ health-related quality of life questionnaires to assess changes in the quality of life. The results of this study will be used to present the evidence needed to request advertising/display allowances, in compliance with the recently amended Cosmetics Act for advertisement in Korea.

**Trial registration:**

Current Controlled Trials ISRCTN46216631

## Background

Dry skin is usually described as a rough, scaly and flaky surface, which worsens under low humidity conditions and often includes sensations of the loss of elasticity and itch [1]. The causes of dry skin are still not fully understood, and a characterisation and definition of this skin disorder have only recently been completed [2,3]. It is also known as a skin-barrier defect and is mainly attributed to a reduction in sebum secretion and consequent loss of water from the stratum corneum (SC). A healthy SC forms an effective permeability barrier that restricts water loss from the body and blocks the penetration of harmful irritants and allergens [4].

Moisturisers are commonly used by both patients with dry skin conditions and people with healthy skin. However, a lack of knowledge persists regarding the effects of moisturisers on skin barrier function [5]. Early studies conducted on individuals with both healthy and diseased skin showed that some moisturisers tend to weaken the skin barrier function, whereas others may strengthen it, and these discrepant results were assumed to be caused by the varied compositions of moisturisers [5].

Complementary and alternative medicine (CAM) has become increasingly popular among skin disease patients. A 2009 national survey study found that 49.4% of patients with a skin problem in the United States had used a CAM treatment within the previous year, and 6% had used one of these treatments specifically for their skin disease [6]. Several herbal medicines have been promoted for ameliorating various dermatological conditions, and some of them, such as propolis, rosemary, sage, sumac and other extracts, are available in topical formulations and cosmetics [7].

*Arctium lappa L.* (Asteraceae), which is commonly known as burdock, has been popularly used to treat inflammatory disorders and various skin problems and could be a candidate herbal remedy for dry skin conditions [8]. Experimental studies have been conducted to find the active ingredients responsible for increasing the blood circulation to the skin surface, improving the skin quality/texture and curing skin diseases [9]. However, to our knowledge, the clinical trial of a moisturiser containing *Arctium lappa L.* has not yet been conducted.

Recently, regulations on cosmetics were heavily revised to ensure safety in South Korea. Especially in terms of advertising, only cosmetics products that have established evidence using clinical trials are allowed to mark and announce their efficacy. Moreover, according to legislation by the Korean Ministry of Food and Drug Safety (KMFDS), moisturisers cannot be recommended for the treatment of skin diseases [10].

The purpose of this study is to establish the basic clinical efficacy and safety of a proposed herbal moisturiser cream containing *Arctium lappa L.* seed extract in healthy people with dry skin conditions. This trial was designed in accordance with the consolidated standards of reporting trials guidelines (CONSORT) and the guidelines for clinical trials of cosmetics products that are aimed at expression and advertisement approval in Korea [11] and will be conducted as a randomised, double-blind, placebo-controlled trial.

## Methods/Design

A randomised, double-blind, placebo-controlled trial will be conducted at the Wonkwang University Oriental Medical Centre in Gunpo, Korea. Participants fulfilling the eligibility criteria will be selected. Enrolled participants will be randomly allocated to one of two parallel groups: the proposed herbal moisturising cream or the placebo cream. Each participant will be examined for signs and symptoms of skin conditions before and after taking the medication. A follow-up to evaluate the long-term safety will be performed via a phone call (Figure 1).

**Figure 1 F1:**
[figure not shown]
Study flow chart.

### Recruitment

We will recruit participants by advertising in local medical centres and on the websites of local medical centres of Gyeonggi province. Respondents will be contacted by clinical trial coordinators (CRC) to determine eligibility via a telephone pre-screen. If an applicant meets the study criteria, he or she will be invited to the clinical research centres to be further examined for eligibility. Korean medicine doctors and internal medicine doctors will conduct the screening together to improve the quality of the eligibility assessment. Korean medicine doctors will manage the screening process. Internal medicine doctors will assess the complete blood cell count (CBC), erythrocyte sedimentation rate (ESR), blood chemistry, urine analysis, and vital signs to exclude patients with serious liver and kidney diseases. Following a pregnancy test, pregnant women will be excluded from the clinical trials.

### Inclusion criteria

Eligible participants of both sexes who are 20 to 65 years of age will be enrolled according to the inclusion and exclusion criteria. We will include participants who present itching or dry skin conditions. The diagnosis of a dry skin condition will be made by the doctor (Korean medicine). Healthy volunteers without skin diseases or any other diseases (acute or chronic) will be enrolled. Participants will be instructed regarding their participation during the run-in, treatment, and follow-up periods. Written informed consent will be obtained from each participant.

### Exclusion criteria

Participants will be excluded if they suffer from any serious medical conditions, such as uncontrolled hypertension, diabetes mellitus requiring insulin injection, past or current malignancy, liver or kidney dysfunction, anaemia, active pulmonary tuberculosis, other severe dermatitis, or any infectious or systemic diseases. The exclusion criteria are as follows: pregnancy, lactation, or planned pregnancy; use of a topical medication containing steroids for the treatment of skin disease more than once per month; participation in the same trial within six months from the interview; hypersensitive skin; skin abnormalities, such as severe acne, erythema, or telangiectasia at the test site; use of the same or similar cosmetics (or pharmaceutical) on the test site within three months of the interview; having undergone a skin peeling or having wrinkles removed within six months of the interview; and any other reasons of unsuitability for the clinical trial at the discretion of the investigator.

Exclusion will be primarily based on information provided by the patients. In addition, additional examinations, such as CBC, ESR, blood chemistry, urine analysis, a pregnancy test, and the assessment of vital signs will be performed before the trial to ensure that the patients do not suffer from any diseases.

We will record the drugs taken by each participant at every visit, and the participants will be asked to notify us of any changes in their medication/supplement regimen. The complete eligibility criteria are provided in Appendix 1.

### Sample size

We wish to estimate the sample size necessary to detect significant differences in skin hydration measured using a Corneometer® 825 (Courage and Khazake, Electronic GmbH, Colongne, Germany) [12], between the experimental and control groups. Sample size was determined based on the results of a recent study [13] in which the mean difference and standard deviation of both groups were 0.94 and 1.22, respectively. The following formula was used to estimate the sample size for a two-group trial:

$$n=\frac{2{\left(Z_{\alpha /2}+Z_{\beta }\right)}^{2}\sigma^{2}}{{\left(\mu_{c}-\mu_{t}\right)}^{2}}$$

Calculations were performed using 80% power, a 5% significance level, and a 20% dropout rate. The required sample size was approximately 27 participants for each group. We plan to enrol 33 participants in each of the two groups to allow for a 20% withdrawal rate, which will ensure that the sample size is in excess of 20, in accordance with the clinical research guidelines of the KMFDS.

### Randomisation and allocation

The randomisation procedure will be guaranteed by Coreana, a consignment organisation. A statistics expert who will have no contact with the study participants will conduct the randomisation of the participants. Participants will be assigned random numbers using a random number generator program (Microsoft Office Excel 2007). These random numbers will be sent to the clinical centre, and the randomisation table will be kept blind by the consignment organisation during the research period. Ultimately, 66 participants will be randomised into two groups. Opaque-sealed envelopes containing serial numbers will be delivered to the clinical centre. An opaque-sealed randomisation table kept by the consignment organisation should be opened as part of the Standard Operating Procedure (SOP). If it has to be opened during an urgent situation involving serious adverse events, the primary investigator must report the incident to the Ethics Committee and the consignment organisation. Before the random assignment, all participants will be informed that they will be assigned to one of two groups. Random allocation will be conducted during the second visit. Random numbers will be matched to their corresponding participants according to the order of the time of second visit. The group assignment results will not be announced to the participants until the last visit of the last participant.

### Blinding

During the trial, investigators will not be in contact with the consignment organisation, the clinical pharmacist, or the statistician. The success of the blinding will be assessed at the last visit of each participant. Researchers who are blinded to the group assignment results will perform the outcome assessment. The blinding procedure will also be verified by the consignment organisation.

### Treatment protocol

Participants will receive the proposed herbal moisturising cream or a placebo cream for four weeks. Application occurs according to the following directions:

Patients in group 1 will receive proposed herbal moisturising cream and instructions on how to apply; they should use an entire packet of the cream (2.00 g) daily. The cream should be applied to the affected areas of skin, to the inner surface of left forearm and to the right side of the face after washing, twice daily (morning and evening), for four weeks.

Patients in group 2 will receive the placebo cream with the same instructions that were provided to group 1.

The defined daily doses (DDDs) of these moisturising creams should be determined based on the specifications and analytical procedures of drug products provided in the KMFDS guidelines. However, no pilot study has previously been reported.

#### Experimental cream

Coreana Cosmetics Co. Ltd. produced the proposed herbal moisturising cream and the placebo cream according to Korea Good Manufacturing Practice (KGMP) standards.

The proposed herbal moisturiser used in this trial is a white, cream-type moisturiser. The proposed herbal moisturising cream is composed of three active ingredients: a controller of sebum biosynthesis; a 70% ethanol extract from the seeds of *Arctium lappa L.*; and vernix caseosa matrix.

#### Placebo cream

Coreana Cosmetics Co. Ltd. developed a homogenous cream that is composed of a base approved by the KMFDS. The colour, form, weight, and scent of the placebo are similar to those of the treatment cream.

### Primary outcome measurement

Skin hydration (Corneometer®), sebum levels (Sebumeter®) and TEWL (Tewameter®) will be assessed as the primary outcome measurements. These parameters will be measured on day 1, day 15 and day 29.

Skin hydration (Corneometer®) will be measured three times at the affected areas of skin, on the inner surface of the left forearm and on right side of the face after washing, and mean values will be adapted for the analysis.

Sebum levels (Sebumeter®) will be measured at the affected areas of skin and on the surfaces of the forehead, cheeks and chin after washing and cleansing (with 70% ethanol). After 60 minutes, the same areas will be measured again, and the differences between two numerical values will be calculated.

After washing, the TEWL (Tewameter®) will be measured three times at the affected areas of skin, on the inner surface of the left forearm and on the right side of the face for 30–50 seconds, and the mean values will be adapted for the analysis.

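### Sebum, a primary outcome, is read at facial sites not limited to the treated right side of the face, so untreated skin can enter the endpoint

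*Protocol article*

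**What the plan says.** Under Treatment protocol, both groups apply their cream to the affected areas and "to the inner surface of left forearm and to the right side of the face after washing, twice daily". No other facial site is named.

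Under Primary outcome measurement, three measures share primary status: "Skin hydration (Corneometer®), sebum levels (Sebumeter®) and TEWL (Tewameter®) will be assessed as the primary outcome measurements". Two of them are read where the cream goes. Besides the affected areas, hydration is read "on the inner surface of the left forearm and on right side of the face after washing, and mean values will be adapted", and TEWL "on the inner surface of the left forearm and on the right side of the face for 30–50 seconds".

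Sebum has a different list: "Sebum levels (Sebumeter®) will be measured at the affected areas of skin and on the surfaces of the forehead, cheeks and chin". The article then says how each sebum value is formed: "After 60 minutes, the same areas will be measured again, and the differences between two numerical values will be calculated". It does not give the side of any facial sebum site or say how the sites are combined. Under Experimental cream, one of the three active ingredients is "a controller of sebum biosynthesis".

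**The concern.** The only facial site named for application is the right half, while the sebum list names cheeks in the plural and two areas, forehead and chin, that cross the midline. A site technician following the text could read sebum on skin that has had neither active nor placebo cream.

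Both arms use the same application sites, so skin without cream is handled identically in both. Unless the cream acts at a distance or is spread across the face, the expected between-arm difference there is zero. Any such reading in the endpoint pulls the comparison toward no difference. A null sebum result could then reflect where the probe was placed and not what the cream does. That matters because the product contains an ingredient aimed at sebum, and because the article's Abstract says the results will support a request for advertising and display allowances.

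**Working it through.** **Sites side by side**

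| Activity | Affected areas | Inner left forearm | Face |
|---|---|---|---|
| Cream applied | yes | yes | right side |
| Hydration read | yes | yes | right side |
| TEWL read | yes | yes | right side |
| Sebum read | yes | not listed | forehead, cheeks, chin; no side given |

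Only the sebum row departs from the application row on the face, and nothing elsewhere in the article resolves the difference.

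**The plan's own figure.** From Sample size: mean difference 0.94, SD 1.22, two-sided 5% level, 80% power. These concern hydration, not sebum.

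- n = 2(1.960 + 0.842)² × 1.22² / 0.94² = 26.44, rounded up to 27 per group. The stated 27 reproduces.
- Standardised effect: d = 0.94 / 1.22 = 0.77.
- Power of the t-test, from the noncentral t distribution with noncentrality d√(n/2) and 2n − 2 degrees of freedom:
  - n = 27: noncentrality 2.83, critical t 2.007, power 0.79.
  - n = 33: noncentrality 3.13, critical t 1.998, power 0.87.

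**Dilution, as an illustration only.** Let f be the treated share of the pooled facial reading. Then

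observed difference = f × (difference on treated skin) + (1 − f) × 0.

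Assumptions: four facial sites (forehead, two cheeks, chin) with equal weight, no effect on untreated skin, unchanged SD, and the hydration d used for want of a sebum figure. The treated share depends on where the probe sits:

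- forehead and chin fully treated, left cheek not: f = (1 + 1 + 1 + 0)/4 = 0.75
- forehead and chin each half treated, left cheek not: f = (0.5 + 0.5 + 1 + 0)/4 = 0.50
- only the right cheek treated: f = (0 + 0 + 1 + 0)/4 = 0.25

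| Treated share f | Effect f × 0.77 | Power, 33 per arm | Power, 27 per arm | n per arm for 80% power, 26.44/f² rounded up |
|---|---|---|---|---|
| 1.00 | 0.77 | 0.87 | 0.79 | 27 |
| 0.75 | 0.58 | 0.64 | 0.55 | 48 |
| 0.50 | 0.39 | 0.34 | 0.28 | 106 |
| 0.25 | 0.19 | 0.12 | 0.11 | 424 |

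The last column uses the plan's normal-approximation formula; the power columns use the noncentral t.

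**Affected areas.** These are treated by definition. If an affected-area reading joined the pool as a fifth equal site, the three shares would rise to (3 + 1)/5 = 0.80, (2 + 1)/5 = 0.60 and (1 + 1)/5 = 0.40. The dilution would be milder but would remain.

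**No pooling.** If each site is analysed on its own, f = 1 at the treated sites and nothing is diluted there. The untreated sites then have an expected difference near zero and still sit under the primary outcome.

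**The case against.** Four points can be made for the plan.

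1. A reader might infer that sebum is certainly read on both cheeks. The text does not say so. The right side of the face contains a right forehead, a right cheek and a right half of the chin, and the sebum list could be naming subregions of the treated half. This stands as a limit: the plural makes a two-sided reading plausible, not certain. The absence of any side, next to two measures that state one, is still a defect in the text.

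2. A reader might infer that treated and untreated readings will be averaged. The article speaks of mean values for hydration and TEWL, but for sebum only of the difference between two readings 60 minutes apart. Combining sites may be settled in a full protocol or analysis plan that is not shown. This stands, so dilution is conditional on pooling.

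3. Cream also goes on the affected areas, which in some participants may include the forehead, chin or left cheek. This stands too, but it does not rescue the endpoint: the treated share of the same nominal sites would then vary from person to person.

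4. A reader might take a fall in power from 0.87 to 0.34 as this trial's loss. It is not. It is one assumed share within a range, on an effect size borrowed from another measure.

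**Conclusion.** The mismatch is in the text and affects one of three primary outcomes; hydration and TEWL are not touched. As written, the sebum readings can include facial skin that receives no cream. Any resulting bias is toward no difference.

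The size cannot be derived, because the article gives no sebum effect size, SD or rule for combining sites. Under the stated assumptions, treated shares of 75% down to 25% put power between about 0.64 and 0.12 at 33 per arm, and between 0.55 and 0.11 at 27 per arm. If every reading is in fact taken on treated skin, there is no loss. The plan's figure of 27 per group, which concerns hydration, is unaffected.

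It is tempting to conclude that the application instruction is right and the sebum site list wrong. The article does not show which of the two departs from what was intended, so that conclusion is not drawn here.

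**What to change.** Reconcile Treatment protocol with Primary outcome measurement so that every site entering the primary sebum analysis is one that receives cream. Which application sites are right is for the sponsor to settle. In the measurement text, state the side of each sebum site and have the spots marked so that days 1, 15 and 29 use the same skin. Keep any reading from untreated skin out of the primary sebum endpoint; it may be reported separately.

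Settle this before the day 1 baseline readings. Values recorded without their side cannot be sorted into treated and untreated afterwards.

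The cost is wording and a site-marking instruction, with no added visits or devices. Fewer readings may contribute to the endpoint, which could make each participant's value somewhat less precise.

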### Secondary outcomes

Secondary outcome measurements include the SC moisture levels (Corneofix®), visual analogue scale (VAS)-xerosis, and VAS-itching. These parameters will be measured on days 1, 15 and 29. The EuroQoL 5-Dimension (EQ-5D), the Health Utilities Index Mark 3 (HUI3), and the Dermatology Life Quality Index (DLQI) will be administered on day 1 and day 29 as measures of the health outcomes. The data collection schedule is detailed in Table 1.

**Table 1 T1:** Data collection schedule

**Period**	**Screening**	**Treatment period**			**Follow-up**
**Visit**	**1st**	**2nd**	**3rd**	**4th**	
	**(D −3)**	**(D 1)**	**(D 15)**	**(D 29)**	**(D 43)**
Informed consent	○				
Demographic characteristics	○				
Medical History	○				
Safety assessment	○	○	○	○	
Skin hydration		○	○	○	
Sebum level		○	○	○	
Transepidermal water loss		○	○	○	
VAS (xerosis, itching)		○	○	○	
Dermatology life quality index		○		○	
EQ-5D		○		○	
Health utilities index mark 3		○		○	
Adverse effects			○	○	○
Blinding assessment				○	

### Patient safety

All patients will undergo routine testing that includes the following assays: CBC, ESR, blood chemistry, pregnancy test, and urine analysis before randomisation and immediately after completing the treatment. Vital signs will be measured at every visit. These tests help identify and exclude patients with serious liver and kidney disease or other severe illness. Investigators will assess a significant result in these tests according to explicit criteria defining the incidence and intensity of adverse events. In addition, pictures of the skin lesions will be recorded as a means of evaluating the adverse events.

